#### Economic assessment

As recommended by the French High Health Authority (HAS), the clinical endpoint used for the cost-utility analysis will be the QALYs (https://www.has-sante.fr/portail/jcms/r_1499251/en/choices-in-methods-for-economic-evaluation). Preference-based utility scores will be calculated using the EQ-5D-5 L questionnaire. The final result of the economic analysis is the incremental cost-utility ratio (ICUR), which expresses the additional costs per additional QALY. The perspective will be that of the society (HAS recommendation). A second analysis will be conducted from the healthcare provider perspective (i.e.*,* hospital). This analysis will take into account the difference between the costs and the tariffs paid for each cost category. The principal economic analysis will be conducted over the time horizon of the IDEAL trial, i.e., 12-month horizon to capture both the immediate and relevant consequences of both the ‘no ileostomy’ and ‘ileostomy’ strategies, which is a period during which all effectiveness and cost data will be precisely collected. To capture the long-term consequences of the intervention compared, we will extend the time horizon of the cost-utility analysis over the patients’ lifetime. The results of the modeling approach will contribute to the decision-making process by comparing our results with other economic analyses conducted in the field of inflammatory bowel disease and investigating long-term survival and costs.

#### Data collection and monitoring

An electronic Case Report Form (eCRF) will collect the patients’ baseline data (sociodemographics, such as current age, age at UC diagnosis, sex, body mass index, weight gain since subtotal colectomy, ASA score, and smoking status; medical history, such as extent of UC, associated primary sclerosing cholangitis, and associated comorbidities; surgical history, such as indications for primary STC, delay between STC and IPAA, postoperative course of subtotal colectomy, and history of other surgical procedures; current and previous treatments, such as anti-TNF, immunosuppressive treatment, and corticosteroid therapy; and baseline QoL assessment, using CGQL and EQ-5D-5 L) as well as perioperative, short- and long-term data according to the abovementioned endpoints. Each patient will participate in the study for 15 months (as there are 12-month data collect points from continuity restoration, which is performed up to 3 months after IPAA in case of defunctioning ileostomy). Clinical reviews will be performed one and 6 months after IPAA and 3 and 12 months after continuity restoration (i.e., either IPAA or stoma closure).

Monitoring will be conducted to ensure that the data are accurate/complete, the safety and rights of subjects are being protected, and the study is conducted in accordance with the applicable regulatory requirements. No deidentified individual clinical trial participant-level data (IPD) will be shared. This monitoring (including data management and data quality insurance) will be ensured by the sponsor. The following monitoring will be conducted: informed consent, deviation of protocol, data collection, and safety and rights of participants. All the eCRFs will be routed to the coordinating center, APHM ([name]). Data entry will be performed using REDCap. Quality assurance will be performed from the final database (data manager). The database will be forward to the statistical team (Aix-Marseille Univ, APHM, Clinic Research Platform). The study information of this protocol has been posted on clinicaltrials.gov. The status of this trial is pending: the first inclusion is estimated for September 1st^,^ 2019.

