## Methods and design

The IDEAL trial is a nationwide prospective, multicenter, open-label, randomized controlled trial in which IBD patients scheduled for completion proctectomy and IPAA will be randomized between having a defunctioning ileostomy (the ‘ileostomy’ strategy) and not having a defunctioning ileostomy (the ‘no ileostomy’ strategy). The study cannot be blinded because the presence of a stoma cannot be simulated and is obvious to both patients and practitioners. The study duration will be 48 months, and the recruitment duration will be 33 months. The study design is summarized in Fig. 1.

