The secondary endpoints are as follows: 6-month major morbidity based on the Clavien-Dindo classification, [14] i.e., number of patients who develop at least one major complication at the 6-month follow-up; 6-month unplanned reoperation rate, i.e., any unplanned abdominal surgery, whether urgent or elective, other than ileostomy closure; 6-month anastomotic leakage rate assessed by a CT scan with an iodine injection, i.e., pelvic abscess, pelvic extradigestive air, pelvic free fluid or pelvic infiltration; 6-month mortality (linked or not with the disease); initial and cumulative 6-month length of hospital stay; 6-month unplanned readmission rate, i.e., other than for ileostomy closure; global and digestive quality of life (QoL) assessed by the Cleveland Global Quality of Life (CGQL) score [15] and the EuroQol Five-levels (EQ-5D-5 L) (i.e., utility values for health states) [16] at baseline and 3 and 12 months from continuity restoration (i.e., either IPAA or ileostomy closure); functional results assessed by the Cleveland Pouch Functional score (PFS) 3 and 12 months from continuity restoration [15]; 12-month pouch results: pouch failure (i.e., with definite ileostomy), anastomotic stricture, pouch in place, and repeat IPAA 12 months from continuity restoration; 12-month global morbidity (i.e., the number of patients who develop at least one complication 12 months from continuity restoration); and 12-month cost-utility analysis, performed 12 months from continuity restoration (cf. *‘* Economic assessment’ below). Though many redo-IPAAs are performed after one year, it is a secondary endpoint and it was felt not relevant enough in this trial to extend its follow-up.

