#### Intervention

An anesthesia consultation is planned before the surgery according to the habits of each department. Participation in the study will not alter the anesthetic procedures. The technical modalities of IPAA are not restricted, but it is mandatory that these modalities are identical in both groups for each center in terms of the type of approach (laparoscopic, single-port, robotic), type of anastomosis (hand-sewn or stapled), pelvic drainage and pouch drainage. Open surgery can be the chosen surgical approach for some patients, provided that a mini-invasive approach cannot be performed due to the surgical history or medical contra-indications, as estimated by the surgeon in charge. A J-pouch will be mandatory as it is the pouch of reference [18].

The defunctioning ileostomy is a covering loop ileostomy, which can be fashioned either in the right or left iliac fossa. The use of an ostomy rod is not mandatory and left to the surgeon’s judgment. Ileostomy closure will be performed 6 to 12 weeks after IPAA as per local protocol or later in case of pelvic sepsis. During stoma closure, the type of ileo-ileal anastomosis (whether end-to-end or side-to-side, hand-sewn or stapled) is not restricted. A CT enema scan can be performed before ileostomy closure to assess the absence of anastomotic leakages, as per the local protocol.

The patients randomized in the experimental group will be treated by completion proctectomy and the creation of an IPAA without a defunctioning ileostomy, which corresponds to a modified two-stage IPAA. As defunctioning ileostomy is omitted in this group, an anastomotic leakage test can be performed when deemed necessary by the surgeon in charge. However, the anastomotic leakage test will not be mandatory.

No concomitant care and interventions are prohibited during the trial.

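### The fixed 15-month participation period does not fit stoma closure later than 12 weeks, so the 12-month visit can fall outside follow-up, mainly for control patients with pelvic sepsis

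*Protocol article*

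**What the plan says.** Four places in the protocol article bear on this.

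- **Data collection and monitoring** fixes the follow-up: "Each patient will participate in the study for 15 months". The reason given is that 12-month data are due from "continuity restoration, which is performed up to 3 months after IPAA in case of defunctioning ileostomy". The same section adds: "Clinical reviews will be performed one and 6 months after IPAA and 3 and 12 months after continuity restoration".
- **Intervention** sets the closure window: "Ileostomy closure will be performed 6 to 12 weeks after IPAA as per local protocol or later in case of pelvic sepsis". No latest date is given for the septic patients.
- **Endpoints** times quality of life (CGQL and EQ-5D-5L) "at baseline and 3 and 12 months from continuity restoration (i.e., either IPAA or ileostomy closure", and lists "functional results assessed by the Cleveland Pouch Functional score (PFS) 3 and 12 months from continuity restoration". Pouch results ("pouch in place, and repeat IPAA 12 months from continuity restoration"), 12-month global morbidity and the cost-utility analysis use the same time origin.
- **Methods and design** sets the calendar: "The study duration will be 48 months, and the recruitment duration will be 33 months".

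**The concern.** The participation period is derived from a closure limit of 3 months that the Intervention section does not impose. A control patient whose closure is delayed by pelvic sepsis can have the 12-month visit fall due after participation has ended. A patient without an ileostomy has continuity restored at the IPAA itself, so that visit falls at month 12, well inside the period, with or without sepsis.

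Pelvic sepsis is the only reason the article gives for closing after 12 weeks, and it can plausibly harm pouch function. Visits lost this way would therefore depend both on arm and on likely outcome. Dropping such patients would make the control mean look better than it is, which would count against the no-ileostomy strategy. The t test or Mann-Whitney test named under Statistical analysis, applied to the observed scores, does not correct for that. EQ-5D-5L also supplies the utilities for the cost-utility analysis.

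**Working it through.** **1. The plan's own figures reproduce.** Latest closure assumed + follow-up = 3 + 12 = 15 months. Recruitment + participation = 33 + 15 = 48 months, the stated study duration. Neither sum contains a reserve.

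**2. Slack for a patient who closes on schedule.** With 30.4375 days per month, 15 months is about 457 days. Closure at 12 weeks plus one year is 84 + 365 = 449 days after IPAA, which leaves about 8 days. This count starts at IPAA. The article does not say when the 15 months start. Under Randomization, inclusion precedes surgery, so a clock started at inclusion leaves less, by an interval that is not given.

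**3. Latest closure that keeps the visit inside 15 months.** 3 × 30.4375 / 7 = 13.0 weeks after IPAA.

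| Closure (weeks after IPAA) | 12-month visit (months after IPAA) |
|---|---|
| 12 | 14.8 |
| 14 | 15.2 |
| 16 | 15.7 |
| 20 | 16.6 |
| 26 | 18.0 |

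**4. Control patients who could be affected.** The target of 194 at 1:1 gives 97 per arm. Leakage with ileostomy serves as a proxy for pelvic sepsis: 8 to 16% under Patient safety, 16.7% in the Background.

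- Ceiling, every patient with a leak closes late: 97 × 0.08 = 7.8 to 97 × 0.167 = 16.2, so about 8 to 16.
- A quarter to a half close late (assumption): 0.25 × 7.8 = 1.9 to 0.5 × 16.2 = 8.1, so about 2 to 8.
- The 15 months is only nominal and just the 48-month calendar binds: with uniform recruitment and closure at 26 weeks (both assumptions), the visit at 18 months is out of reach only for those recruited in the last 3 of 33 months, or 9%. Of 8 to 16 patients that is 0.7 to 1.5, about 1. With closure at 16 weeks the share is 0.7/33, about 2%.

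In the no-ileostomy arm the corresponding number is 0 if continuity restoration means the IPAA.

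**5. Shift in the control mean.** If a fraction f of the arm is missing and those patients score d SD worse than the rest, the observed mean exceeds the true one by f × d. The article gives no value for d; 0.5 to 1 SD is an assumption.

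- 2 of 97, d = 0.5: 0.021 × 0.5 = 0.01 SD
- 8 of 97, d = 1: 0.082 × 1 = 0.08 SD
- 16 of 97, d = 1 (ceiling): 0.165 × 1 = 0.16 SD

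**The case against.** The strongest reply is that no visit is ever said to be cancelled. The 15 months is a derived figure, and the visit schedule follows actual closure. A site could treat 15 months as nominal and see the patient at the due date, in which case only the 48-month limit binds and about one patient is affected. This stands as to size: the number lost depends on how strictly the 15 months is applied. It does not remove the conflict, because the period is stated for each patient and the calendar total is built on it.

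The size also deserves caution. Leakage is not the same as sepsis that delays closure past 13 weeks; the Endpoints definition of leakage includes CT findings such as pelvic free fluid. The 16.7% comes from a cohort of IBD patients having IPAA, not specifically completion proctectomy, for which the Discussion expects a lower leak risk. Against a standard error of about √(2/88) = 0.15 SD for a difference between arms of 88, a shift of 0.01 to 0.08 SD is small.

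A reader might infer that all septic control patients lose the visit, that no experimental patient can, and that the comparison is certainly biased. The article supports none of these. Septic patients who close by about 13 weeks stay inside the period. An experimental patient given a secondary stoma after a leak might also have a late continuity restoration, and the text does not settle how that patient is timed. The direction of bias is therefore probable, not established.

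Finally, visit windows and the handling of late visits are details that a condensed article may leave to the full protocol. Their absence is not the point here. The point is that two stated rules do not agree.

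**Conclusion.** The conflict is real. A 15-month period resting on closure within 3 months cannot hold a 12-month visit counted from a closure that the article allows to be later, and the 48-month total gives no reserve for the last recruits. Any loss would fall mainly on control patients with pelvic sepsis and would probably favour the control arm.

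The number lost ranges from about 1 to a ceiling of 16 of 97 according to how the 15 months is applied and how many patients close late, neither of which the article settles. The effect on the control mean is likely to be small, and its size rests on the assumed late-closing share and score deficit. What is exposed is limited to the secondary 12-month endpoints (CGQL, EQ-5D-5L, PFS, pouch results, global morbidity) and the cost-utility analysis. The primary endpoint is timed at 6 months from proctectomy and is untouched. The point should be corrected, but it does not threaten the trial's main conclusion.

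**What to change.** Reconcile Methods and design, Intervention, and Data collection and monitoring:

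- Define the end of participation as the 12-month visit after actual continuity restoration, instead of a fixed 15 months, and state when the clock starts.
- State an outer limit, counted from IPAA and applied in both arms, at which any patient who has not reached that visit is assessed: CGQL and EQ-5D-5L, and PFS if the pouch is in use.
- State which date counts as continuity restoration for a no-ileostomy patient who receives a secondary stoma.
- Extend the 48-month study duration to match the outer limit.

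No change to the rule for stoma closure is proposed. The cost is protocol wording, some months of added follow-up for a few patients and a slightly later last visit. No patients or procedures are added.

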#### Patient safety

A safety analysis will be performed by an independent monitoring committee based on the anastomotic leakage rate in the experimental group (i.e., “no ileostomy” group): the chosen threshold will be 15%, as it represents a 30% higher rate of anastomotic leakage compared to the available rates in the literature for cases of completion proctectomy with ileostomy (8 to 16%) [7, 8, 12]. The management of amendments to the protocol and adverse events will follow the procedures of the regulatory department of the sponsor.

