An old randomized study from 1992 included 45 patients with no corticosteroid treatment and compared systematic ileostomy during IPAA and no ileostomy. Half of the patients in each group had STC, and the postoperative morbidity was 52% in the “ileostomy” group vs. 32% in the “no ileostomy” group (including an SBO incidence of 22% in the “ileostomy” group vs. 9% in the “no ileostomy” group). These differences were not significant, but the number of patients was small, and these results did not take into account the morbidity of ileostomy closure. Moreover, the mean hospital length of stay (LOS) was significantly longer in the “ileostomy” group than in the in the “no ileostomy” group when both IPAA and ileostomy closure were assessed [6].

More recently, some retrospective case-controlled studies have assessed one-stage IPAA (i.e., total proctocolectomy and IPAA without ileostomy) [11, 12]. The morbidity was comparable between patients who underwent one-stage and those who underwent traditional two-stage IPAA. However, the majority of the patients had FAP, not IBD; all IBD patients were carefully selected, and none received corticosteroid medication. Thus, these results cannot be extended to all colonic IBD patients. Interestingly, a retrospective study emanating from international tertiary care centers found that a “modified” two-stage procedure might be the best option for IBD patients who are at high risk for postoperative morbidity [7]. Namely, Sahami et al. compared 305 IBD patients undergoing IPAA with defunctioning ileostomy to 316 patients undergoing IPAA without defunctioning ileostomy. The rate of anastomotic leakage was not influenced by the ileostomy (ileostomy 16.7% vs. no ileostomy 17.1%, *p* = 0.92), but the ileostomy group presented with more SBO in the long term than the no ileostomy group (ileostomy 18.9% vs. no ileostomy 10.3%, *p* = 0.003). Defunctioning ileostomy was an independent risk factor for SBO (OR = 2.58 CI_95%_[1.5–4.7]). Moreover, the risk of pouch failure over time was similar between the two groups in the Kaplan-Meier analysis.

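### The 15% leak threshold is justified as 30% above literature rates of 8 to 16%, but it lies inside that range and is a 30% excess only over an unstated baseline of 11.5%

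*Protocol article*

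**What the plan says.** Under Patient safety, an independent committee is to carry out a safety analysis "based on the anastomotic leakage rate in the experimental group". The section states that "the chosen threshold will be 15%, as it represents a 30% higher rate of anastomotic leakage compared to the available rates in the literature", and describes those rates as being "for cases of completion proctectomy with ileostomy (8 to 16%) [7, 8, 12"]. No single baseline within that range is named. This is the only numeric safety threshold in the article.

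The Background describes the retrospective study cited there as reference 7, which compared "305 IBD patients undergoing IPAA with defunctioning ileostomy to 316 patients undergoing IPAA without defunctioning ileostomy". It reports leak rates of "ileostomy 16.7% vs. no ileostomy 17.1"% and concludes that the stoma made no difference to leakage. Reference 7 is one of the three sources cited for the 8 to 16% range.

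Under Endpoints, the 6-month anastomotic leakage rate is a secondary endpoint, compared between the two groups.

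**The concern.** A threshold described as 30% higher than a set of reference rates should lie above the rates it refers to. This one lies within them, so the sentence does not tell the committee what excess a 15% leak rate represents. Depending on where the true rate with ileostomy falls in the stated range, 15% could be nearly double the expected rate or slightly below it.

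This matters because the Discussion treats the leak rate without a stoma as a principal worry about the experimental strategy. A committee relying on the stated derivation could be alarmed by a rate that the protocol's own sources report with a stoma. It could also be reassured by a rate that is well above a low baseline.

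**Working it through.** **Inputs.** Threshold 15%, stated excess 30% and reference range 8 to 16% (Patient safety). Leak rates of 16.7% with and 17.1% without ileostomy (Background). 88 patients per group and 194 in total (Statistical analysis). Allocation is 1:1 (Methods and design), so 194 / 2 = 97 in the experimental arm.

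**Step 1: try to reproduce 15%.** A 30% relative excess is 1.3 × baseline.

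| Baseline | 1.3 × baseline | 15% / baseline |
|---|---|---|
| 8% (lower end) | 10.4% | 1.875 (88% above) |
| 12% (midpoint) | 15.6% | 1.25 (25% above) |
| 16% (upper end) | 20.8% | 0.94 (6% below) |
| 16.7% (Background, with ileostomy) | 21.7% | 0.90 (10% below) |

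Solving backwards, 15% / 1.3 = 11.5%. Reading the 30% as percentage points gives 38% to 46%, so that is not what was meant. The stated figure is reproduced only from a baseline of 11.5%, which the article does not give.

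**Step 2: compare with the Background.** 15% is below both 16.7% and 17.1%. The 16.7% is also above the 16% given under Patient safety as the upper end, although reference 7 is cited for that range.

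**Step 3: what the ambiguity means in practice.** The article gives no decision rule, so one is assumed for illustration: a single look, with a flag if the observed rate is 15% or more. With n = 97, 0.15 × 97 = 14.55, so the flag needs 15 leaks. With n = 88, 0.15 × 88 = 13.2, so it needs 14. The exact binomial probabilities of a flag, P(X ≥ 15) and P(X ≥ 14), are:

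| Baseline | True rate | Situation | n = 97 | n = 88 |
|---|---|---|---|---|
| 8% | 8% | no excess | 1% | 1% |
| 8% | 10.4% | 30% excess | 7.7% | 7.0% |
| 12% | 12% | no excess | 18% | 17% |
| 12% | 15.6% | 30% excess | 56% | 51% |
| 16% | 16% | no excess | 60% | 55% |
| 16% | 20.8% | 30% excess | 93% | 90% |

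If the rates in the Background applied to this trial, the probability of a flag would be 67% at 16.7% and 71% at 17.1% (n = 97).

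**Sensitivity to the assumed rule.** Suppose instead that the flag required the one-sided 95% exact lower bound to exceed 15%, which needs 22 leaks in 97. The arm would then be flagged 5% of the time at a true 16%, 36% at 20.8%, and less than 0.1% at 10.4%. The error rates therefore depend on the rule. The mismatch in Step 1 does not.

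**The case against.** The best defence is that a central baseline was meant. The midpoint of 12% gives 15.6%, and 11.5% gives 15.0%, so 15% may well be a rounded 30% excess over a middle value. That is plausible, and it means the value itself need not be wrong. It is still an inference: the text sets the 30% against the whole range and names no central rate.

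A reader might infer that the upper end of the range is misquoted, because the Background gives 16.7%. The document does not establish this. The 16.7% is for ileal pouch-anal anastomosis in inflammatory bowel disease generally, whereas the range is said to be for completion proctectomy, where the Discussion argues that leak risk is lower. Whether 16% is a subgroup figure, another source's figure or a truncated 16.7% cannot be told from the article. The two sections need reconciling, but the point stands on the printed 16% alone.

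A reader might also infer that the rule fails in both directions at once. It does not. The likely false flag needs a baseline near the upper end and the likely miss needs one near the lower end. At a 16% baseline, a 30% excess is flagged about 93% of the time.

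Finally, the missing minimum number of patients, interval and schedule of looks might seem to be a fault. These may sit in the full protocol or the committee's charter, and an article commonly leaves them there, so they are not counted. Nor does the article say that crossing 15% stops anything.

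**Conclusion.** The point holds as a fault in the stated derivation. On the article's own figures, 15% is not 30% above 8 to 16%. It lies inside that range, and it is a 30% excess only over an unstated 11.5%. This is arithmetic and rests on no assumption.

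The practical size is conditional. It assumes one look, a flag at an observed 15% or more, and 97 (or 88) evaluable experimental patients. On those terms there is about a 60% (55%) chance of a flag with no excess if the true rate is 16%, and about an 8% (7%) chance of flagging a 30% excess over 8%. Repeated looks would raise these chances, but the article gives no schedule, so none is modelled.

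The documents do not show that 15% is the wrong value; they show that its stated reason does not support it. The primary endpoint, its analysis and the sample size are unaffected. Severity: should-fix.

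**What to change.** Reconcile the Background and Patient safety sections on the leak rate with ileostomy, saying which population and source each figure describes. State the single baseline to which the 30% refers. Then recompute the threshold from that baseline, or give another justification for it. Have the committee read the experimental-arm rate beside the concurrent leak rate in the ileostomy arm, so that a high rate common to both arms is not taken for an effect of omitting the stoma. The value is for the committee and sponsor to decide, and none is proposed here.

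The cost is a reworded paragraph and a matching line in the committee's working documents. The ileostomy-arm leak rate is already collected as a secondary endpoint, so no extra patients, visits or procedures are needed.
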